Broader healthcare system issues exacerbate these challenges. Doherty et al. [9] identified several systemic barriers in primary care, including inadequate provider training, poor communication, and limited involvement of people with MID in decision-making. These barriers contribute to fragmented care and exclusion from essential services. Addressing these issues requires tailored addiction programs alongside systemic reforms, such as enhanced provider training, accessible communication strategies, and collaborative decision-making. Among the various barriers, low treatment motivation emerges as a particularly pivotal and modifiable factor. Research has shown that individuals with MID often experience limited insight into their substance use, struggle to articulate personal goals, and have difficulties initiating and sustaining treatment engagement [10, 11]. Motivation is a key predictor of treatment adherence and success across populations [12], and in the MID population it is closely linked to the quality of relational support and the extent to which autonomy, competence, and relatedness are supported [13]. However, most substance abuse services are not designed to foster these conditions.

As such, motivational barriers are not simply part of a broader problem—they are a core obstacle to effective care, and one that must be addressed first in order to enable access and engagement with treatment. This forms the rationale for the Beat the Kick intervention, which explicitly targets motivation as the primary outcome. Beat the Kick aims to strengthen autonomous motivation using approaches grounded in motivational interviewing and self-determination theory. By addressing this critical barrier, Beat the Kick seeks to create the conditions under which other forms of support can become accessible and effective.

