## Intervention

### Explanation for the choice of comparators {6b}

The comparator in this study is the CAU condition. This choice enables a direct evaluation of the effectiveness of the Beat the Kick intervention relative to the standard care typically provided to people with MID and substance abuse problems. Participants in the CAU group will receive support from their intellectual disability healthcare organization, which may involve a multidisciplinary team including physicians, nurses, psychologists, social workers, and counselors.

Standard care in the CAU group encompasses a wide range of approaches tailored to individual needs. These may involve techniques to enhance readiness for change, as well as strategies focused on building supportive relationships between the individual and their caregiver. The aim is to create a stable and safe environment in which individuals feel valued and engaged in meaningful daily activities that foster a sense of competence and reduce challenging behaviors. Standard care may also include guidance, information, and assistance related to substance use and intellectual disabilities, along with regular check-ups to monitor progress, assess needs, and provide general support. Participants in the CAU group will not receive the structured Beat the Kick intervention. However, they will continue to receive care from their regular healthcare providers, including support related to substance use and intellectual disabilities. This ensures that all participants receive an ethically appropriate level of baseline care while allowing for a valid comparison with the added value of the intervention.

In addition, the use of a CAU comparator rather than a waitlist control helps prevent bias that could arise from nocebo effects. Participants placed on a waitlist may experience demoralization, reduced motivation, or worsening of symptoms due to the absence of support, which can artificially inflate the intervention’s observed effectiveness. By comparing Beat the Kick to the care that is actually available in practice, the study maintains both clinical relevance and methodological integrity.

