### Intervention description {11a}

The Beat the Kick intervention consists of ten weekly individualized sessions, each lasting 45–60 min, designed to help participants understand and change their substance abuse patterns, identify triggers, and adopt healthier coping strategies. The intervention draws upon Self-Determination Theory [26] and Motivational Interviewing [33] to foster autonomous motivation. It does so by supporting the basic psychological needs of autonomy, competence, and relatedness, and by creating a safe, supportive environment in which participants are encouraged to explore and commit to meaningful behavior change.

Each participant is guided by a healthcare professional who has completed the “Train the Trainers: Beat the Kick” program. The program begins with an introductory session in which the trainer builds rapport, discusses expectations, and tailors the intervention to the participant’s specific needs and circumstances. To prevent potential carry-over effects, staff members supporting participants in the intervention group will not simultaneously support participants in the CAU group. This separation ensures that intervention-specific knowledge and techniques are not inadvertently applied in the control condition, preserving the integrity of the comparison.

Subsequent sessions are structured thematically. The second and third sessions help participants explore their substance use behaviors and attitudes through interactive activities such as online assignments, video clips, and discussions. Concepts like the distinction between substance addiction and substance abuse are clarified with visual aids. In sessions four through six, cognitive-behavioral techniques are introduced using the ABC model [34], which links triggers, beliefs, and behaviors. These sessions focus on identifying craving triggers and developing healthier responses.

Session seven emphasizes identifying personal values and interests to explore alternative activities that can replace substance use, while session eight focuses on evaluating the participant’s social network and identifying individuals who can offer support during challenging moments. The final two sessions consolidate the learnings by developing a personalized action plan and discussing options for ongoing support. The program concludes with a certificate recognizing participants’ efforts.

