### Criteria for discontinuing or modifying allocated interventions {11b}

Participants may discontinue the intervention for various reasons. They are free to withdraw from the study at any time without providing an explanation, and their autonomy in making this decision will be fully respected. If a participant’s condition deteriorates, for example due to increased substance use, the onset of severe psychiatric symptoms, or emerging safety concerns, healthcare professionals may advise discontinuation of the intervention in order to safeguard the participant’s well-being.

Discontinuation may also be considered if the participant experiences substantial emotional distress or other adverse effects that appear to be directly related to the intervention. In situations where participants consistently miss sessions or have difficulty engaging with the intervention, additional support will be offered to promote continued involvement. Whenever possible, modifications will be made in collaboration with the participant and their caregiver to enhance engagement, rather than opting for discontinuation. All forms of discontinuation, including partial disengagement such as repeated absences or reduced participation, will be documented and may be analyzed as outcomes in their own right. These instances may provide valuable insight into motivational dynamics or barriers to sustained participation.

If a participant voluntarily initiates formal addiction treatment during the study period, this will be recorded as a meaningful outcome rather than treated as a reason for discontinuation. This step will be interpreted as an indication of increased autonomous motivation to change, provided the decision to seek treatment is made voluntarily and not due to external pressure.

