### Outcomes {12}

The primary outcome is the change in autonomous motivation for substance-abuse treatment, measured using an adapted version of the TSRQ [21]. The TSRQ comprises 15 items rated on a 5-point Likert scale (1 = completely untrue; 5 = completely true). Subscales are scored as means (range 1–5) and include autonomous motivation (internal consistency α≈0.84; primary endpoint), controlled motivation (α≈0.78), and amotivation (α≈0.41; analyzed exploratorily due to lower reliability). As participation in the intervention and any subsequent treatment is voluntary, baseline motivation may be relatively high; this will be considered when interpreting change. Assessments will occur at pre-treatment (T1), post-treatment (T2), and follow-ups at 1 month (T3) and 6 months (T4), with the primary endpoint defined as Δ(T2–T1) on autonomous motivation and maintenance examined at T3/T4. To optimize comprehension for MID/BIF participants, all self-reports will be interviewer-assisted.

Secondary outcomes include reductions in substance use and related problems, measured with the SumID-Q (patterns, frequency, consequences), which embeds the AUDIT and DUDIT screens. The AUDIT has 10 items (item scores 0–4; total 0–40) with commonly used cut-offs ≥ 8 for hazardous use and ≥ 20 for probable dependence. The DUDIT has 11 items (item scores 0–4; total 0–44) with cut-offs for hazardous use of ≥ 6 for men and ≥ 2 for women, and ≥ 25 for probable dependence. Both continuous totals and categorical classifications (none/hazardous/probable dependence) will be analyzed at T1, T2, T3, and T4 (recall periods per instrument guidance). Psychological need satisfaction and frustration will be assessed with the Basic Psychological Needs Satisfaction and Frustration Scale – Intellectual Disabilities (BPNSFS-ID; 24 items, 5-point Likert), yielding mean scores (range 1–5) for autonomy, competence, and relatedness (higher satisfaction = greater fulfillment; higher frustration = greater need thwarting) at T1, T2, T3, and T4 [35].

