## Statistical methods

### Statistical methods for primary and secondary outcomes {20a}

Data analysis will be conducted using R version 4.5.0 or later [41], following standard procedures for descriptive and inferential analyses.

The primary objective of this RCT is to assess the effectiveness of the Beat the Kick intervention compared to CAU in enhancing autonomous motivation for substance abuse treatment among adults with MID. It is hypothesized that participants in the Beat the Kick group will exhibit greater improvement in autonomous motivation from pre-test to post-test compared to the CAU group, with an anticipated medium effect size.

Linear mixed models (LMM) will be employed to test this primary hypothesis using the lme4 package in R [42]. LMMs are particularly suited for repeated measures data, accommodating both fixed and random effects [42]. Models will include fixed effects for group (Beat the Kick vs CAU), time (T1–T4), and the group × time interaction (primary effect of interest), with random intercepts and random slopes for time at the participant level to capture individual trajectories. The randomization stratification variable “addiction type” (alcohol vs cannabis/other drugs) will be included as a fixed effect in all models to adjust for baseline heterogeneity between strata; exploratory interaction terms with group and time (e.g., group × time × addiction type) will be examined to assess effect modification [43]. Baseline outcome values will serve as covariates to control for initial differences, mitigating regression to the mean [44].

Analyses will primarily adhere to the intention-to-treat (ITT) principle, preserving the integrity of randomization and providing a conservative estimate of the intervention’s effectiveness [45]. This approach ensures that all participants are analyzed in their originally assigned groups, irrespective of adherence or dropout. Complementary per-protocol (PP) analyses will also be conducted for participants who completed the intervention as intended, providing additional insights. Missing data will be handled using maximum likelihood estimation, a robust method that assumes data are missing at random, leveraging all available information without requiring imputation [46].

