Descriptive statistics will summarize baseline characteristics and outcome variables, including autonomous motivation and substance use levels. The normality of continuous variables will be assessed using the Shapiro-Wilk test [48] and visual inspection of histograms and Q-Q plots. Rather than applying data transformations or switching to non-parametric tests that may reduce interpretability and statistical power, linear mixed models will be retained even when normality assumptions are violated. This decision is supported by recent simulation research demonstrating the robustness of linear models to non-normal data, particularly in the context of hypothesis testing [49]. To safeguard validity, diagnostic checks (e.g., Cook’s distance, leverage values) will be conducted to detect influential data points. Where necessary, sensitivity analyses will be performed with and without such points to assess their impact on the results.

To ensure reliability and validity, Cronbach’s alpha will assess the internal consistency of scales [50], while intraclass correlation coefficients (ICCs) will evaluate reliability across repeated measures [51]. The results section will detail the statistical techniques employed, including maximum likelihood estimation for incomplete data [52], and highlight how LMMs effectively capture fixed and random effects, providing insights into individual variability and longitudinal trends. This rigorous methodology supports robust and interpretable findings (Table 3).

**Table 3 Tab3:** Statistical analysis

	**Measure**	**Type of data**	**Timepoints**	**Statistical analysis**	**Subjects**
Motivation and psychological needs	TSRQ	Continuous	4	Linear Mixed Models	ITT, PP
	BPNSFS-ID	Continuous	4	Linear Mixed Models	ITT, PP
Substance use	SumID-Q	Continuous	4	Linear Mixed Models	ITT, PP

*ITT*, intention-to-treat analysis, including all randomized participants in the analysis; *PP*, per-protocol analysis, focusing on participants who adhered strictly to the protocol

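### The per-protocol analysis selects on programme completion, which only the Beat the Kick arm can meet, so it can (but need not) show a benefit when there is none

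*Protocol article*

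**What the plan says.** Section {20a} of the protocol article makes ITT the main analysis: "Analyses will primarily adhere to the intention-to-treat (ITT) principle, preserving the integrity of randomization". It then adds: "Complementary per-protocol (PP) analyses will also be conducted for participants who completed the intervention as intended, providing additional insights". Table 3 lists both analyses for the TSRQ, the BPNSFS-ID and the SumID-Q. Its footnote describes the second one differently, as a "per-protocol analysis, focusing on participants who adhered strictly to the protocol".

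The two arms differ in what can be completed. Section {11a} states: "The Beat the Kick intervention consists of ten weekly individualized sessions, each lasting 45–60 min". Section {6b} states: "Participants in the CAU group will not receive the structured Beat the Kick intervention". Neither {20a} nor the footnote gives a criterion that a CAU participant would have to meet.

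The article also comments on who adheres and who stops:
- The background on barriers to treatment says: "Motivation is a key predictor of treatment adherence and success across populations".
- Section {11b} says of repeated absences and reduced participation: "These instances may provide valuable insight into motivational dynamics or barriers to sustained participation".
- Section {11b} also says that professionals may advise stopping if a participant deteriorates, and gives increased substance use as an example.

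Motivation is the primary outcome, "with the primary endpoint defined as Δ(T2–T1) on autonomous motivation" (section {12}).

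**The concern.** Read as {20a} words it, the per-protocol set compares a selected part of the Beat the Kick arm with the whole CAU arm. A Beat the Kick participant who loses motivation, or whose use rises, can leave the set. A CAU participant with the same course has no programme to leave. Where completion depends on how the outcome develops after baseline, the two groups differ even if the programme does nothing. Adjusting for baseline factors does not remove that difference.

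The result would be reported next to ITT for three scales. Section {20a} calls ITT conservative and the per-protocol analysis a source of further insight. A reader may therefore take a larger per-protocol figure as the effect of actually receiving the programme.

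**Working it through.** **Inputs from the article (section {14} unless stated).** Effect size f = 0.25, which is d = 0.5 for two groups; correlation among repeated measures ρ = 0.5; four measurements; dropout about 40%; 69 per arm (section {8}).

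**The plan's own figure.** For a between-groups repeated-measures ANOVA, λ = f²·N·m / (1 + (m − 1)ρ) = 0.0625 × 82 × 4 / 2.5 = 8.2. With 1 and 80 degrees of freedom the power is 0.808, so N = 82 reproduces. Then 82 / 0.6 = 136.7, which gives 137, or 138 for equal arms. The sample size is not in question here; it supplies only ρ and the planned 0.5 SD.

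**Assumptions not in the article.**
- Completion of 60%. The only 40% in the article is study dropout, so this is a stand-in for non-completion; 50% and 80% are shown as well.
- r, the correlation of the propensity to complete with the part of T2 motivation that T1 does not explain. The article gives no value.

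**Formula.** With a true effect of zero and the filter in one arm only, the bias in total-SD units is

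r × √(1 − ρ²) × φ(z) / p,

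where p is the proportion completing and z the matching normal quantile. For p = 0.6, φ(0.253) / 0.6 = 0.644, and √0.75 = 0.866, so the bias is 0.558 × r. The factor 0.866 is needed because r refers to residual variation. Without it the results would be 0.13, 0.19 and 0.32 residual SD, which cannot be set against a planned 0.5 total SD.

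**Results.** Simulation: 69 randomised per arm, 5,000 runs per cell, T2 adjusted for T1. This is simpler than the planned mixed model.

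| Completing | r | Bias, formula (SD) | Bias, simulated (SD) | Type I error |
|---|---|---|---|---|
| 60% | 0 | 0.00 | 0.00 | 5.2% |
| 60% | 0.2 | 0.11 | 0.11 | 10.3% |
| 60% | 0.3 | 0.17 | 0.17 | 15.9% |
| 60% | 0.5 | 0.28 | 0.28 | 38.5% |
| 80% | 0.3 | 0.09 | 0.09 | 8.2% |
| 50% | 0.3 | 0.21 | 0.20 | 19.4% |

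Against 0.5 SD, the 60% rows with r from 0.2 to 0.5 run from 0.11 / 0.5 = 22% to 0.28 / 0.5 = 56% of the planned effect.

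**When the bias vanishes or reverses.**
- Completion tracks baseline motivation only (correlation 0.3 to 0.5, 60% completing): the bias is 0.00 SD with baseline adjustment. On the change score it is (ρ − 1) × 0.644 × 0.3 = −0.10 SD to (ρ − 1) × 0.644 × 0.5 = −0.16 SD, against the intervention.
- The same filter applied to both arms (60% completing, both correlations 0.3): bias 0.00 SD, type I error 4.7%. The cause is therefore the one-arm filter.

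**The case against.** Several points on the other side carry weight.

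- **ITT is primary.** The per-protocol analysis is called complementary, and no confirmatory claim rests on it. This stands and limits the importance of the point.
- **A reader might infer that the per-protocol analysis is bound to favour Beat the Kick.** The documents do not support that. Section {11b} says only that disengagement may be informative about motivation, and names distress, psychiatric symptoms and safety among the reasons for stopping. The Discussion adds verbal ability, living conditions and caregiver availability. If completion follows baseline motivation only, the planned baseline adjustment removes the bias.
- **The covariates include living arrangements and prior treatment.** These may absorb some selection, but they are baseline factors and do not reach selection on later change.
- **The Table 3 footnote could cover both arms.** Strict adherence to the protocol is a looser test than completing the intervention, so an unfiltered CAU group is an inference from {20a}. But the footnote states no CAU criterion either, and the two wordings differ. The exact session threshold may properly be left to the analysis plan and is not criticised here.
- **A reader might extend the point to every outcome.** Table 3 covers three scales only; treatment engagement, referral follow-through and acceptability are not in it.
- **An instrumental-variable estimate with full completion as exposure would fit badly.** Partial attenders receive sessions, and the staff briefing and the helper in {11a} may act without completion. This stands and shapes the fix.

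**Conclusion.** The point holds as a minor one. As {20a} is worded, the per-protocol comparison is not randomised, because its filter exists in one arm and the article links adherence and stopping to motivation and to substance use. It can produce a benefit on the TSRQ, BPNSFS-ID and SumID-Q without any effect, but it need not.

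The range of about 0.11 to 0.28 SD was worked out for motivation. It rests on two assumed quantities, 60% completion and r between 0.2 and 0.5, and on an unfiltered CAU arm. At r = 0, where completion is unrelated to the course after baseline, the bias is nil after baseline adjustment. The documents cannot say where in this range the trial will fall. The ITT result is unaffected.

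**What to change.** In section {20a} and Table 3, make the complement to ITT a complier-average (instrumental-variable) estimate:
- Instrument: randomised arm. Exposure: having started the programme, meaning any session attended. Use number of sessions as a sensitivity analysis.
- Since CAU has no access to the programme, the estimate is in essence the ITT difference divided by the proportion who start. It stays at zero when the ITT effect is zero.
- State the exclusion restriction openly, including that the staff briefing and the helper might act on people who attend no session.
- State that the estimate relies on outcome data from those who stop. Section {18b} plans this only for those who agree to stay in the study.

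Reconcile the {20a} wording of the per-protocol set with the Table 3 footnote. If the completer contrast is kept, report it as descriptive and open to selection bias.

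The cost is a short scripted model and a few sentences, with no new participants or measurements. The downside is more assumptions to state and an interval wider than that for ITT by roughly one over the proportion exposed: 1 / 0.8 = 1.25 times at 80%, 1 / 0.6 = 1.67 times at 60%.

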### Interim analyses {21b}

No interim analyses are planned for this study. Decisions regarding early trial termination will be based solely on safety considerations or clear evidence of harm or benefit, as determined by the ethics committee.

### Methods for additional analyses (e.g., subgroup analyses) {20b}

Subgroup analyses will evaluate the intervention’s effects based on participants’ living arrangements (e.g., 24-h supervised care, outpatient services, or home-based support) to determine whether the care context moderates effectiveness. To minimize contamination or carry-over effects, staff members supporting participants in the intervention group will not be assigned to clients in the CAU group. In cases where overlap is unavoidable, measures will be taken to monitor and control for potential contamination effects in the analyses.

Additional subgroup analyses will explore whether the intervention’s effectiveness differs between individuals with MID and those with BIF, acknowledging potential differences in cognitive, communicative, and contextual resources between these groups.

The analysis will also consider the impact of prior exposure to substance use treatment, including the number and type of previous treatments. Demographic factors such as gender and age will be evaluated for potential moderating effects. Furthermore, patterns of substance use (alcohol and cannabis) will be assessed to determine whether specific use profiles influence the intervention’s effectiveness. This comprehensive approach aims to provide deeper insights into the factors shaping the intervention’s impact, guiding adaptations for specific populations and care settings.

